#### Intervention group

Several key elements of the intervention must be highlighted:
Clinical data will be reviewed and registered by FPs in the electronic case report forms (eCRF) after recruitment in baseline visit.Because of the natural separation between actual electronic health records and electronic case report forms developed for the research project, final tool has been integrated into a dedicated eCRF system using a webservice WS4 version 1.2 of the CheckTheMeds® tool with the specific inputs reviewed by the FPs. This avoids barriers for FPs and the need for reintroducing double information to a separate system. Simple and detailed review of treatment plans has been incorporated. Simple review webservice outputs have been agreed after a Delphi technique with relevant stakeholders (primary care pharmacist, hospital pharmacist, family physicians, and researchers).The web-based, user-initiated DSS provide FPs with drug-therapy information that is relevant to participating patients with polypharmacy on demand. After verifying the clinical data included in the eCRF (multimorbidity and polypharmacy corrected for patient-specific factors such as sex, renal function, age and frailty), this DSS provides health professionals with clinical scenarios to optimize treatment plans for patients, the number of STOPP/START and Beers criteria, drug interactions classified based on their potential severity (traffic light system), and adjustment of the medications to other relevant clinical variables.FPs will be able to add and modify patient data in eCRF and able to review again treatment plans as many times as needed with up-to-date relevant information (new drugs, new diagnoses, change if laboratory findings about kidney function, etc.).A specific training tool with video-recorded examples for clinical scenarios with treatment plans reviews appearing on first access to the tool and available for revising when needed as part of the formative intervention.

There are no restrictions regarding concomitant care during the trial. This intervention was developed in accordance with the recommendations and the taxonomy proposed by the Cochrane Effective Practice and Organization of Care Group (EPOC). The intervention is described in detail in Fig. 2, following the approach proposed by Perera et al. and the Template for Intervention Description and Replication (TIDieR) (Additional file 3) [38]..

**Fig. 2 Fig2:**
[figure not shown]
Intervention

### Control group

The patients in the control group will receive the usual clinical care based on the provision of advice and information and will be subjected to the examinations recommended in the guideline corresponding to each of the chronic diseases presented by the patient. Physicians will receive the same initial training programme as professionals in the intervention group.

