**Objective:**

To assess the effectiveness and cost-effectiveness of the complex intervention MULTIPAP Plus, compared to usual care, in improving prescriptions for young-old patients (65-74 years old) with multimorbidity and polypharmacy in primary care.

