**Intervention:**

Complex intervention based on the ARIADNE principles with three components: (1) family physician (FP) training, (2) FP-patient interview, and (3) decision-making support system.

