## Aim

### Primary

The main objective is to evaluate the effectiveness of the complex intervention MULTIPAP Plus, in improving prescriptions to a young-old population (65–74 years) with multimorbidity and polypharmacy measured with a composite endpoint of hospital admission or death at 18 months, compared with usual care.

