### Randomization

The unit of randomization is the FP, and the unit of analysis is the patient. The randomization of FPs will be achieved using the treatment assignment module of Epidat® 4.1; the proposed intervention will be considered the treatment, and usual care will be considered the control. To guarantee an equal number of FPs in each group (intervention and control), the option “balanced groups” will be selected. Once all participating FPs have selected their patients and have collected the corresponding initial data, the Research Unit, Primary Care Management of Madrid, will randomize them centrally. Subsequently, each FP will receive the information of the study group to which they have been assigned, at which time all the patients they have recruited will be included in that group.

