### Intervention

This is a complex intervention that includes the training of FPs and physician-patient interview based on the Ariadne principles; the effectiveness of the intervention has been studied in the MULTIPAP RCT [23, 36, 37]. The training includes activities related to basic concepts of multimorbidity, the appropriateness of prescriptions, adherence to treatment, the ARIADNE principles, and shared doctor-patient decision-making. All participating physicians will receive this training with the objective of incorporating patient-centred interviews into their routine clinical practice. This would allow the effect of the training to be isolated from the use of a DSS.

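### The objectives compare the three-component package with usual care, but both arms get the FP training, so only the arm-specific components on top of common training are tested

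*Protocol article*

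**What the plan says.** The abstract describes the intervention as having "three components: (1) family physician (FP) training, (2) FP-patient interview, and (3) decision-making support system". Its objective is "To assess the effectiveness and cost-effectiveness of the complex intervention MULTIPAP Plus, compared to usual care". The primary aim repeats this: "The main objective is to evaluate the effectiveness of the complex intervention MULTIPAP Plus", "measured with a composite endpoint of hospital admission or death at 18 months, compared with usual care". The second secondary aim sets the cost-utility ratio against usual care as well, and the Randomization section labels the arms the same way: "the proposed intervention will be considered the treatment, and usual care will be considered the control".

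The sections on what each arm receives say something else. Under Control group: "Physicians will receive the same initial training programme as professionals in the intervention group". Under Intervention, every participating physician is trained, with the aim that patient-centred interviewing becomes routine practice, and the reason given is: "This would allow the effect of the training to be isolated from the use of a DSS". The Discussion confirms that all physicians are trained beforehand and presents this as a way to reduce performance bias.

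The cost-utility paragraph under Secondary outcome variables lists training time and teaching staff among the costs incurred, alongside interview time and the licence for the tool.

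**The concern.** A two-arm trial estimates the difference between what its two arms receive. Here one of the three named components is given to both arms, and a second, the patient-centred interview, is at least partly shared because the common training is meant to instil it. The stated question is therefore not the one the randomisation answers.

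This affects the conclusions. If the result is positive, the stated objective credits the whole package, training included, with a benefit that training did not contribute to the contrast. If the result is null, the same wording says the package failed against usual care, when no group received untrained usual care. In the economic analysis, costs shared by both arms would be set against a benefit that reflects only what differs between them.

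**Working it through.** **1. Content of each arm, as the article describes it.**

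| Component | Intervention arm | Control arm | Source |
|---|---|---|---|
| Initial FP training | yes | yes, the same | Intervention; Control group; Discussion |
| Patient-centred interview | yes | to the extent the common training changes practice | Intervention; abstract |
| DSS in the eCRF | yes | not during follow-up | Intervention group; Discussion |
| Video training for the tool | yes | no | Intervention group |
| Patient intervention at 6, 12 and 18 months | yes | not listed | Table 1 |
| FP intervention around randomisation | yes | not listed | Table 1 |

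The last row fits poorly with the first. If it means the common training, it contradicts the three sections that give that training to everyone. If it means the tool training, Table 1 should say so.

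**2. What the contrast identifies.** Let R be the 18-month risk under untrained usual care, t the reduction due to common training, and a the further reduction due to the arm-specific components given that training.

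- Control risk: R − t
- Intervention risk: R − t − a
- Randomised difference: (R − t) − (R − t − a) = a
- Package against untrained usual care: R − (R − t − a) = t + a

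No arm has risk R, so neither t nor t + a can be estimated from the randomised data. Covariate adjustment or a multilevel model does not change this. Common training therefore separates the arm-specific effect from the training effect, but it does not provide an estimate of the training effect.

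**3. The plan's effect size.** The Sample size section gives 16% incidence, a difference of six percentage points, 80% power and 5% alpha. Taking 16% against 10%, two-sided, with mean 13%:

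n = [1.960 × √(2 × 0.13 × 0.87) + 0.842 × √(0.16 × 0.84 + 0.10 × 0.90)]² / 0.06² = (0.932 + 0.399)² / 0.0036 ≈ 492 per arm.

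This reproduces the printed 492. The section states the six points as a difference between the study groups, which is a in step 2. The figure does not conflict with the design. It only needs to be tied to the trained-control comparison.

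**4. The cost-utility ratio.** Let C_T be the common training cost per arm, C_A the cost of the arm-specific components, S the avoided costs and ΔQ the between-arm QALY gain.

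- Costs as listed, charged to the intervention: (C_T + C_A − S) / ΔQ
- Incremental between arms: [(C_T + C_A − S) − C_T] / ΔQ = (C_A − S) / ΔQ
- Excess: C_T / ΔQ

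For a positive ΔQ, the listed method makes the intervention look less favourable than the trial's own comparison would. The article gives no unit costs or expected QALY gain, so the excess cannot be put in euros.

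**The case against.** The strongest reply is that shared training is deliberate and disclosed. The Intervention section gives its purpose, the Control group section describes its delivery and the Discussion defends it, so usual care in the objectives can be read as shorthand for the control condition defined later. Randomisation, endpoint and between-arm analysis all remain valid. All of that stands, and the design is defensible as an add-on trial. But it confirms that the contrast is an increment over training, while the objectives, the cost-utility aim and the randomisation text name a different comparison. The shorthand also does not cover the cost list, which counts training as an intervention cost.

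A reader might infer that the trial tests the DSS alone. The article does not support that: Table 1 lists an FP intervention and a patient intervention for the intervention group only, and the Intervention group section adds training specific to the tool. Fig. 2 and the TIDieR file, which may settle the exact content of each arm, are not available here.

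A reader might also infer that the 16% and the six points belong to the package question, so that the trial is underpowered for what it really tests. That is not supported either. The six points are stated as a difference between the study groups. The 16% comes from earlier studies, and the article does not say whether their physicians were trained. Any split of the six points between training and the rest would be invented.

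**Conclusion.** The point holds as an inconsistency between the stated question and the randomised contrast. Training is a defined component of MULTIPAP Plus and is given equally to both arms, so the trial estimates the arm-specific components on top of common training and cannot estimate the package against untrained usual care. This follows from the article's own description of the arms and needs no numerical assumption.

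The point concerns what may be concluded and how incremental cost is formed. It does not show bias in the between-arm effect estimate or a loss of power. The overstatement of the cost-utility ratio, C_T / ΔQ, assumes that the listed training costs are charged to the intervention arm without an equal charge to control, which is how the cost paragraph reads. How much of the interview differs between arms remains open.

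**What to change.** 1. Restate the primary objective, the abstract objective, the cost-utility aim and the arm labels under Randomization along these lines: *the intervention-arm components (DSS-supported treatment review, its tool training and the intervention-only patient intervention) added to common FP training, compared with usual care by FPs given the same training.*
2. Reconcile Table 1's FP intervention row, marked for the intervention group, with the sections that give training to all physicians. State which interview elements, if any, are delivered in one arm only.
3. Add a sentence under Sample size saying that the six-point difference refers to this between-arm contrast.
4. State that the effect of the whole package against untrained usual care is not estimated and will not be claimed.
5. In the cost list and in the calculation of the cost-utility ratio, leave the common training out of incremental cost or count it equally in both arms. Keep the tool-specific training as an intervention cost.

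The cost is a narrower claim, edits to wording, and keeping common and tool-specific training costs separate. Recruitment, randomisation, data collection and the planned sample size are unaffected by this point.

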### Blinding

Due to the type of intervention, neither FPs and their patients nor the MULTIPAP Plus study team was blinded to the treatment allocation.

### Variables

FPs will provide their data before the start of the study. Patient data will be collected by the recruiting FP, who will also be responsible for patient follow-up. All information will be recorded in a case report form designed for the study. Each FP will access the form from their personal computer through the project website using a personal identification code. Four visits were defined for patient data collection: baseline (T0), 6 months (T1), 12 months (T2), and 18 months (T3) (see Table 1).

**Table 1 Tab1:** Visit plan

	T0 (baseline)		T1 (6 m*)	T2 (12 m*)	T3 (18 m*)	Responsible entity
Confirm inclusion/exclusion criteria	X					FP
Written informed consent	X					FP
Sociodemographic variables	X					FP
Morbidity variables and drug treatment plan	X		X	X	X	FP
Randomization of FP´s		X				RU
FP intervention (intervention group)		X				RT
Patient intervention (intervention group)			X	X	X	FP
Mortality				X	X	RT/FP
Hospitalizations				X	X	RT/FP
Functionality (WHODAS), falls, hip fractures			X	X	X	FP
Use of health services			X	X	X	RT
Quality of life	X			X	X	FP
Usability, adhesion, satisfaction			X		X	TG
Costs					X	RT

*T* time, *FP* family physician, *RU* research unit, *IG* intervention group, *RT* research team, *TG* technical group, *m** months from randomization

#### Primary outcome variable

The primary outcome is a composite endpoint of hospital admission or death during the observation period measured as a binary outcome. Primary outcome measures are recorded by the FPs when they occur or at follow-up visits.

#### Secondary outcome variables

All cause mortality, non-elective hospital admission (number of episodes and duration)Related to the use of medication: Potentially inappropriate prescription will be evaluated in accordance with the BEER criteria [39] and the STOPP-START criteria [40]; medication safety will be measured as the incidence of adverse reactions and potentially dangerous interactions, classified based on the taxonomy proposed by Otero-López [41] as well as the incidence of adverse reactions; and adherence to treatment will be measured. Medication adherence was measured with the Morisky Medication Adherence score [42].Use of health services will be measured using records of unplanned and/or preventable hospitalizations as well as the use of emergency services and PC (FP and nurse).Quality of life will be measured using the EQ-5D-5L questionnaire [43, 44]. The differences in utility index between the intervention group and the control group at 18 months of follow-up will be used to determine the QALYs gained due to the intervention. The scores or utilities derived from the latest version of this tool, the EQ-5D-5L, have been proposed to provide information on economic evaluations of technologies.Disability will be measured using the WHODAS questionnaire [45] and number of fractures.For cost-utility, the National Health Service perspective will be adopted, with a time horizon of 2 years and a discount rate of 3%. The costs incurred will be the time dedicated to training required by the training programmes, the cost of the teaching staff, the time dedicated to doctor-patient interviews, and the rights to use of the tool (DSS). All costs derived from the intervention will be charged through an opportunity cost proxy: average salary by professional category. As “avoided costs” of the intervention, we will consider the price of the drugs discontinued (measured using the retail price) and the cost of the adverse reactions avoided. The EQ-5D-5L questionnaire will be used to estimate the utilities in both groups (intervention and control). The QALYs obtained with the intervention will be calculated and compared with the difference between the costs incurred and avoided.DSS usability will be measured from user analysis perspective and usability testing [46] to the direct users (FPs): (a) User analysis: this analyses user behaviour while interacting with a website. It is going to be realized non-obtrusively in the background by recording mouse movements and click behaviour to identify to what extent functions and website areas are accessed when reviewing treatments (Hotjar Tool); (b) usability using an ad hoc design with the Spanish-validated System Usability Scale (SUS) [47] and Computer Software Usability Questionnaire [48], DSS acceptability will be measured using records of actions performed with the CheckTheMeds® algorithm (number of changes) and a review of time invested per professional, and DSS satisfaction will be measured using an ad hoc questionnaire.

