## Methods

### Design

Pragmatic parallel two-arm, superiority, community-based cluster-randomized controlled clinical trial with a follow-up of 18 months. The unit of randomization is the FP, and the unit of analysis is the patient. The cost-utility study will be carried out from the perspective of the Spanish National Health System with a time horizon of 2 years.

CONSERVE-SPIRIT has been used for reporting trial protocol instead of SPIRIT since MULTIPAP Plus had been suspended because of COVID-19 from March 2020 to May 2021 and methodologic modifications were made (Additional file 1: CONSERVE-SPIRIT checklist; Additional file 2: SPIRIT Trial Modifications in Extenuating Circumstance). This situation has been notified and updated in the trial registry.

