#### Analysis of secondary effectiveness

The same analysis will be performed for 12 months. Missing data for professionals and/or patients will be replaced with the most recent reference or available data. For the remaining secondary effectiveness analyses, the difference in means or proportions will be calculated based on the characteristics of the variables (T3−T0) and (T2−T0) between groups using the appropriate statistical tests, and an explanatory model will be adjusted using the same methodology applied to the main outcome variable.

*Estimated quality-adjusted life years (QALYs)* gained at the population level, with corresponding 95% CI, as determined using parametric methods and bootstrap techniques. Given the 2-year time horizon, a discount rate of 3% will be applied.

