## Discussion

This pragmatic clinical trial will involve the participation of FPs from over 130 PC health centres in different geographic areas of Spain, thus ensuring a high level of external validity, given that the PC model implemented throughout the country is relatively homogeneous.

Among the possible limitations or biases of our study, we take into consideration that professionals who agree to participate may be more motivated, leading to observer bias (Hawthorne effect). Those professionals more involved in the work will probably make greater use of the DSS than if it were established under normal conditions. If the tool is effective, we might observe an overestimation of the effect that if applied to routine clinical practice would be more limited. This could lead to a greater effectiveness than would be obtained under normal conditions, but it is expected that when randomization is performed after the inclusion of patients in the study, the magnitude of the difference between the two groups will be minimized. Additionally, all physicians will have previously received the training intervention. In this way, it will be ensured that all physicians receive the same training and share the same knowledge of the study, thus reducing performance bias.

The use of a composite endpoint as hospital admission or death is proposed as recommended by some European studies, in order to compare the results with these studies [28, 60, 61].

The intervention cannot be blinded, which could influence the results. However, because the variables can be obtained from records, those who carry out the analysis and their interpretation will not know to which group the patient belongs. In turn, to avoid possible contamination of the professionals in the control group, the intervention group will be advised of their commitment to confidentiality. The control group may use the DSS to review the treatments of the patients included in the study at the end of follow-up for a similar period of time. The expected changes in quality of life are small, but their measurement allows incorporating outcome variables reported by the patient and calculating utilities.

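### QALYs gained are tied to the utility difference at month 18, which is not accumulated utility, and the 2-year horizon runs six months past the data with no stated extrapolation rule

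*Protocol article*

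**What the plan says.** **QALY rule.** Under Secondary outcome variables, the article gives this rule for QALYs gained: "differences in utility index between the intervention group and the control group at 18 months of follow-up will be used to determine the QALYs". The same section says that EQ-5D-5L supplies the utilities in both groups and that the QALYs obtained are set against the net costs.

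**When utility is measured.** Table 1 marks quality of life at T0 (baseline), T2 (12 months) and T3 (18 months), but not at T1. Costs are marked at T3.

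**Horizon.** The Design section describes a "cluster-randomized controlled clinical trial with a follow-up of 18 months" and plans the cost-utility study "from the perspective of the Spanish National Health System with a time horizon of 2 years". Analysis of secondary effectiveness repeats the longer horizon: "Given the 2-year time horizon, a discount rate of 3% will be applied". Table 1 has no visit after month 18.

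**After follow-up.** The Discussion adds: "The control group may use the DSS to review the treatments of the patients included in the study at the end of follow-up".

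**Uncertainty.** QALYs get confidence intervals from parametric and bootstrap methods. Calculation of the cost-utility ratio varies costs over their range of uncertainty and QALYs within their 95% confidence intervals.

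**The concern.** A QALY gain is the area between the two arms' utility curves over time. The stated rule uses the height of the gap at the last visit. Height and area agree only for particular time courses, and the article gives no reason to expect one of these.

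Two further gaps follow from the wording. A raw difference at month 18 carries any chance imbalance in baseline utility with it. And a patient who dies before month 18 has no month-18 utility, so the rule as written assigns that patient no value, in a trial whose primary outcome includes death.

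The horizon is a separate problem. The last half-year is unobserved, nothing says how it is filled, and the randomised contrast is not protected there because controls are permitted to use the decision support system.

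Cost-effectiveness is part of the stated objective, QALYs are the denominator of the ratio, and the Discussion expects only small changes in quality of life. The way QALYs are computed could therefore decide the reported ratio.

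**Working it through.** The article gives no utility difference, QALY gain or cost-utility ratio, so there is no stated figure to reproduce.

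**Inputs from the article:** utility at 0, 1 and 1.5 years (Table 1); follow-up 1.5 years; horizon 2 years; discount rate 3%.

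**Assumptions:** straight lines between visits; no discounting in the main comparison; equal baselines unless stated; the month-18 difference multiplied by 1.5 years, because the article states no multiplier. The ratios do not depend on the size of the effect.

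**Step 1. Area over 18 months.** With between-arm differences d0, d12 and d18:

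area = 1 × (d0 + d12)/2 + 0.5 × (d12 + d18)/2

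E is the size of the difference in each pattern.

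| Pattern | d0, d12, d18 | Area | 1.5 × d18 | Ratio |
|---|---|---|---|---|
| Linear rise | 0, 2E/3, E | 0.333E + 0.417E = 0.75E | 1.5E | 2.0 |
| Complete by month 12, then held | 0, E, E | 0.5E + 0.5E = 1.0E | 1.5E | 1.5 |
| Only after month 12 | 0, 0, E | 0 + 0.25E = 0.25E | 1.5E | 6.0 |
| Halved between months 12 and 18 | 0, E, E/2 | 0.5E + 0.375E = 0.875E | 0.75E | 0.86 |
| Gone by month 18 | 0, E, 0 | 0.5E + 0.25E = 0.75E | 0 | 0 |

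**Step 2. Does the conclusion depend on the multiplier of 1.5?** No. In units of the month-18 difference, the area is 0.75, 1.0, 0.25 and 1.75 (0.875E ÷ 0.5E) in the first four rows. In the last row that difference is zero while the area is not. No single multiplier fits them all.

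**Step 3. Baseline imbalance.** Suppose a difference of 0.03 (illustrative) exists at baseline and stays there with no treatment effect. The rule gives 0.03 × 1.5 = 0.045 QALY. After subtracting the baseline difference, the gain is 0.045 − 0.045 = 0.

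**Step 4. Months 19–24.** These are 6/24 = 25% of the horizon. For the linear rise, with area 0.75E at month 18:

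- difference lost at month 18: 0.75E + 0 = 0.75E
- fading linearly to zero by month 24: 0.75E + 0.25E = 1.0E
- held to month 24: 0.75E + 0.5E = 1.25E

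The unobserved half-year thus adds between 0 and 0.5E/0.75E = 67% of the 18-month gain. At an illustrative E = 0.03 that is 0 to 0.015 QALY on top of 0.0225.

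**Step 5. Discounting.** At 3%, second-year values are scaled by about 1/1.03 = 0.97, which does not offset any of the above.

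**The case against.** The best defence is that an article condenses the full plan. The sentence gives no formula and does not expressly exclude the baseline and 12-month values. An area-under-curve calculation could be set out in a fuller document, and so could the handling of deaths. This stands in part. A reader might infer that month 18 alone will be used, or that deaths will be excluded; neither is stated. What the article does state is a rule that names one visit, and that rule is open to correction as written.

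A second defence is that Analysis of secondary effectiveness plans T3−T0 and T2−T0 contrasts and a model built like that for the main outcome, with baseline variables and a random physician effect. But those contrasts are for the remaining secondary outcomes, and QALYs have their own paragraph without them. A change score at one visit is still not accumulated utility: with equal baselines, the ratios above are unchanged.

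A third is that bootstrap intervals and multivariate sensitivity analysis are planned. These vary the chosen estimate within its uncertainty. They neither change what is estimated nor supply values for months 19–24.

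Finally, a horizon longer than follow-up is not in itself an error, and control use of the tool is permitted, not certain. Both points are right. What is missing is the rule that carries the estimate past month 18.

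**Conclusion.** The point holds for the secondary cost-utility analysis. The stated QALY rule does not measure accumulated utility, and the horizon exceeds the data by six months without an extrapolation rule.

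On the assumption of a 1.5-year multiplier, the rule gives from 0 to 6 times the area-under-curve gain across the patterns shown. For fixed costs, cost per QALY moves inversely: a gain counted at 2.0 times its size halves it. Months 19–24 could add 0% to 67% of the 18-month gain in the linear case. The differences of 0.03 are illustrative only.

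Three stronger readings go beyond the article:

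- **That the gain will be overstated.** An early effect that fades would be understated, so the direction is not known.
- **That a 2-year multiplier inflates the gain 2.7 times.** That divides 2E by the 18-month area of 0.75E and is like for like only if the effect vanishes at month 18. With the difference held, 2E/1.25E = 1.6; with a fade to month 24, 2E/1.0E = 2.0.
- **That the error is as large as the gain the trial seeks, or that the comparator is lost after month 18.** No target QALY gain is given, and control access is optional.

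**What to change.** 1. Compute each patient's QALYs as the area under the utility curve from T0, T2 and T3, with utility 0 from the date of death.
2. Compare arms in the multilevel model, adjusted for T0 utility and with a random physician effect.
3. Report the 18-month within-trial result, for costs and QALYs alike, as the main cost-utility analysis.
4. Report the 2-year result as a labelled extrapolation with stated scenarios for months 19–24: difference lost, fading, and held.

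The cost is a little more analysis work and a shorter main horizon. The utility measurements and mortality follow-up are already scheduled, so no new visit is needed.
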